## Abstract

**Background/Objectives**: Necrotizing enterocolitis (NEC) is an inflammatory disease with an incidence of about one in 1000 live births, much higher in premature and low birth weight newborns. Intestinal dysbiosis is an important element in the pathogenesis of NEC, and for this reason, experimental models have been used to administer fecal microbiota transplants (FMTs) for prophylaxis and treatment of NEC with very satisfactory results. The primary endpoint of the study is safety, defined as the incidence of adverse events (AEs) and serious adverse events (SAEs) occurring from the time of intervention until hospital discharge, classified according to severity and assessed for relatedness to the intervention. **Methods**: This prospective, single-arm, open-label clinical study will include 20 infants born between 24 0/7 and 36 6/7 weeks of gestation. FMTs will be administered twice as a deep rectal infusion via a Foley catheter. The donors of the material from which the FMT will be prepared will be women in the third trimester of pregnancy. The safety of the therapy will be assessed by comparison with a control group, i.e., 20 patients who will meet the same inclusion criteria and will not meet any of the exclusion criteria, subject to the same hospital observation but without undergoing any medical/therapeutic intervention other than the collection of biological material. **Discussion**: The study will provide data on the safety and initial efficacy of FMT in this group of patients, which will allow for further research into the use of this method in the prevention of infections and NEC. Ethics: The study protocol was approved by the Bioethics Committee of the Medical University of Warsaw, Warsaw, Poland (KB/52/2025). All procedures will follow the principles of the Declaration of Helsinki. The results of the study will be submitted for knowledge translation in peer-reviewed journals and presented at national and international pediatric society conferences. Clinical Trial Registration: The study is registered at ClinicalTrials.gov: ID: NCT06333405.

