#### 2.3.4. Inclusion Criteria

Premature babies born naturally or by caesarean section between 24 0/7 and 36 6/7 weeks of pregnancy.At least 24 h after the end of antibiotic therapy, if it is/was used.Up to 6 days of age OR up to 14 days of age in the case of transfer from another facility or temporary contraindications to the administration of microbiota (defined below).Newborns born in the hospital conducting the experiment and outside of it.Premature infants hospitalized in the intensive care unit and neonatal pathology unit during the study period.Signed informed consent of parents/legal guardians for the child’s participation in the experiment in the study group (with the administration of microbiota)—in the version for newborns born between 24 0/7 and 27 6/7 weeks of pregnancy.B. Signed informed consent of parents/legal guardians for the child’s participation in the experiment in the study group (with microbiota administration)—version for newborns born between 28 0/7 and 36 6/7 weeks of gestation.C. Signed informed consent of parents/legal guardians for the child’s participation in the experiment in the control group (without administration of microbiota)—in the version for the control group.

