## 4. Detailed Procedure

### 4.1. Transplant Recipients Procedures

FMT will be administered to patients in the study group who meet the inclusion criteria and do not meet the exclusion criteria, in the form of a deep rectal infusion, in a volume of 5 mL, twice at 6 h intervals, between 3 and 6 days after birth and/or up to 14 days in patients who experience temporary contraindications to the use of FMT or in patients who will be transferred to our center for treatment from an external facility.

In the first phase of the experiment, 10 patients from the study group born between 28 0/7 and 36 6/7 will undergo the procedure. All adverse effects of the therapy will be monitored and documented on an ongoing basis. If no serious adverse events (SAEs) occur, we will include another 10 patients born between 24 0/7 and 27 6/7 in the study (phase two of the experiment).

A serious adverse event (SAE) is defined as any medical event that, at any dose, meets at least one of the following criteria:Leads to death.Is life-threatening to the participant.Requires hospitalization or prolongs hospitalization.Leads to permanent or significant impairment of function or disability.A detailed description of the monitored parameters is provided below.

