### 4.4. Procedures for the Patients in the Control Group

Check whether the patient meets the inclusion criteria for the experiment.Check whether the patient meets the exclusion criteria.Discuss the purpose and procedures of the experiment with the patient’s parents/guardians and obtain their informed consent for the child’s participation in the experiment. This includes consent for the processing of personal data and the use of biological material samples for scientific purposes, as well as consent for participation in surveys and follow-up on the effectiveness of therapy.Collect blood parameters indicating inflammation (leukocytosis, CRP, procalcitonin) at the “0” point (“BEFORE intervention”), between signing the consent form and the fifth day of the child’s life.Ensure that biological material samples (feces, urine and blood samples) are collected before (point “0”) FMT, as described in the section below, or collect samples before the sixth day of the child’s life.For the control group, the matching time point for administering gut microbiota doses and counting “post” days is assumed to be the sixth day of the child’s life.From day 6 (the matching time point), any adverse events or deviations from the norm will be recorded, such as deterioration in general condition, appearance of symptoms of infection or increase in inflammation indicators.Blood inflammation parameters (leukocytosis, C-reactive protein (CRP), procalcitonin) will be collected during the “post-matching time point” period at least once within 72 h of day 6, or more frequently if the patient’s clinical condition requires it, as assessed by the attending physician.

The following will also be recorded in both study groups:-The number of days spent in hospital;-Percentage increase in body weight (birth weight vs. weight at discharge);-The number of days of antibiotic therapy received during hospitalization (monitoring until discharge from the hospital conducting the experiment).

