### 5.2. Secondary Outcomes

The following parameters will also be analyzed:-Duration of hospitalization.-Weight gain (percentage increase from birth to discharge).-Length of antibiotic therapy.-Incidence of other infectious or inflammatory complications.

The collected biological material will also enable the exploratory analysis of microbiota composition and its changes throughout the experiment.

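### Antibiotic days are counted over the whole hospital stay, so days before FMT, which FMT cannot affect, enter a between-group secondary outcome

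*Protocol article*

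**What the plan says.** All references are to the protocol article.

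- **Antibiotic count (section 4.4, both groups):** "The number of days of antibiotic therapy received during hospitalization (monitoring until discharge from the hospital conducting the experiment". The count covers the hospitalization; no start at FMT or at the matching time point is given.
- **Secondary outcome (section 5.2):** "Length of antibiotic therapy", again without a starting point.
- **Prior antibiotics (section 2.3.4):** allowed, on the condition "At least 24 h after the end of antibiotic therapy, if it is/was used".
- **Timing of FMT (section 4.1):** "between 3 and 6 days after birth and/or up to 14 days in patients who experience temporary contraindications". The later limit also applies to infants transferred in.
- **Adverse events, for contrast:** the Abstract counts those "occurring from the time of intervention until hospital discharge". For controls, section 4.4 says "From day 6 (the matching time point), any adverse events or deviations from the norm will be recorded".
- **Analysis (section 2.3.3):** continuous variables are compared between groups by t-test or Mann–Whitney U test, and interpretation rests mainly on effect estimates with 95% confidence intervals.
- **Control matching time point:** sections 2.3.6 onward let it be postponed up to day 14 on the same grounds as FMT. Sections 4.4, 4.5 and Table 1 set it at day 6 of life.

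**The concern.** A treatment can change only what happens after it is given. A course that ended a day or more before FMT1 is a baseline fact about the infant, yet the stated window adds it to the outcome. The protocol has a time zero for each arm and uses it for adverse events, but not for antibiotic days.

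Two things are at stake. First, early courses vary between infants for reasons unrelated to FMT, which widens the confidence interval on which interpretation is meant to rest. Second, allocation alternates by order of admission, is unblinded and uses a separate consent form for each group (sections 2.3.2 and 2.3.4). Section 5.4 itself concedes possible selection bias and residual confounding. Any difference between the groups in early antibiotic use passes straight into the estimated difference.

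Infants transferred in add a further ambiguity. The text says where antibiotic monitoring ends, but not whether days at the referring hospital belong to the total.

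**Working it through.** The article states no expected number of antibiotic days, standard deviation or power, so there is no figure of its own to reproduce.

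**1. Largest pre-FMT exposure.** Inputs: last scheduled dosing day 6, latest dosing day 14 (section 4.1), and 24 h off antibiotics (section 2.3.4). Ceiling = dosing day − 1.
- Dosing by day 6: 6 − 1 = about 5 days.
- Dosing on day 14 (postponed or transferred infants only): 14 − 1 = about 13 days.

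These are ceilings, not expected values.

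**2. What the total measures.** Let A be antibiotic days before the index point and B those after it. The difference in mean totals is (difference in mean A) + (difference in mean B). FMT can act only on the second term.
- One infant at the ceiling adds 5/20 = 0.25 day, or 13/20 = 0.65 day, to the mean of an arm of 20.
- If mean A is equal in the two arms, the first term is zero and A adds only variance. If it is not, the whole imbalance goes into the result.

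**3. Size of the noise (illustration; both SDs assumed).** If A and B are independent, the SD of the total is √(SD_B² + SD_A²), and the confidence interval widens by √(1 + SD_A²/SD_B²). Power for a true difference of 0.8 × SD_B with n = 20 per arm (normal approximation) is Φ(difference / (SD × √(2/20)) − 1.96).
- B only: 0.8/0.3162 = 2.530; Φ(0.570) = 72%.
- Example with SD_B = 3 and SD_A = 2: SD = √13 = 3.606; 2.4/(3.606 × 0.3162) = 2.105; Φ(0.145) = 56%; interval wider by 3.606/3 = 1.20.

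| SD_B (days) | SD_A = 1 | SD_A = 2 | SD_A = 4 |
|---|---|---|---|
| 3 | 67% (×1.05) | 56% (×1.20) | 33% (×1.67) |
| 5 | 70% (×1.02) | 65% (×1.08) | 51% (×1.28) |
| 8 | 71% (×1.01) | 69% (×1.03) | 62% (×1.12) |

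Entries are power on the whole-stay total, with the widening of the interval in brackets. The loss is negligible when later antibiotic use varies much more than early use, and material when it does not.

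**4. Why the control index point comes first.** Suppose controls start on day 6 and study infants at FMT1. For the same discharge day, an infant dosed on day 3 is counted for 6 − 3 = 3 days more than a control, and one dosed on day 14 for 14 − 6 = 8 days fewer. Also, a study infant on antibiotics on day 6 is postponed, so that course falls before the index point. If day 6 is fixed for controls, the same course in a control falls after it.

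**5. Deaths.** The Introduction gives NEC risks of 9–13% and NEC mortality of 15–30%. Multiplied: 9% × 15% = 1.35% to 13% × 30% = 3.9% per infant, or 20 × 0.0135 = 0.27 to 20 × 0.039 = 0.78 expected NEC deaths per 20 infants. The NEC risks refer to infants of up to 32 weeks or with heart disease, so they are likely too high for the more mature infants here. All-cause mortality is not given. A death in the trial is plausible enough for its reporting to matter.

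**The case against.** The case for leaving the text alone has four parts.

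- *Pre-FMT days occur in both arms under the same antibiotic criterion.* This is correct and limits the point: the main effect is noise, and bias needs an actual difference in early use.
- *Infection after FMT is measured more directly elsewhere.* Also correct. Section 4.3 follows NEC, positive blood cultures and antibiotic use for 72 h after FMT, section 5.1 puts symptoms of infection in the primary outcome, and section 5.2 lists infectious complications. Antibiotic days are not the main infection measure.
- *A whole-stay count avoids unequal starting ages.* This stands as long as the control time point is unsettled, and it is why that has to be reconciled first. It does not justify counting days that FMT cannot affect.
- *The study is an unpowered pilot whose limitations are acknowledged.* True, but interpretation rests on estimates and intervals, which are what the window degrades.

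A reader might go further and infer that antibiotic days and hospital days both stop at death or transfer, so that an early death scores as a good result. The documents do not support this. They do not say how a death enters either outcome, and that is commonly left to an analysis plan. The end at discharge from the trial hospital is written for antibiotic days only; "The number of days spent in hospital" in section 4.4 and "Duration of hospitalization" in section 5.2 carry no such limit. Death is a serious adverse event and counts in the primary endpoint. Any figure for days of distortion due to deaths would need a mean stay, a day of death and a mortality that the article does not give.

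**Conclusion.** The point holds for the antibiotic-day window. As written, the secondary outcome includes up to about 5 antibiotic days per infant, and at most about 13 with dosing on day 14, that are complete before FMT. This follows from the article's own timing rules without further assumption.

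The consequence is mainly loss of precision. Under the assumed SDs above, the interval widens by between 1% and 67%. There is bias only if the two groups differ in early antibiotic use, which alternate allocation does not rule out. The primary endpoint is unaffected because it already has a starting point. The change is worth making because it is cheap and brings this outcome into line with how adverse events are counted.

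**What to change.** 1. **Reconcile the control matching time point.** Sections 2.3.6 onward make it postponable; sections 4.4, 4.5 and Table 1 fix it at day 6. State one rule, such that both arms start counting at comparable ages.
2. **Sections 4.4 and 5.2:** for the between-group comparison, count antibiotic days from the index point (FMT1 in the study group, the matching time point in controls).
3. **Baseline:** report antibiotic days before the index point as a baseline characteristic by group, including those at a referring hospital where known.
4. **Deaths:** report deaths by group next to antibiotic days and length of stay, so that a short count due to death is not read as benefit.

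Cost: a few lines of wording, and antibiotic start and stop dates on the case report form instead of a single total. No additional infants, visits or samples are needed.

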### 4.5. Protocol for Collecting Biological Samples from Both Groups for Safety and Exploratory Analyses

Biological material samples will be collected from patients in both groups (study and control) before FMT1 and after FMT2 at the following time points: 0, 7, 14, 30, 60 and 120 days after FMT2. These samples will be used for therapy safety analysis and exploratory analyses (e.g., microbiota analysis). Ideally, these samples will be blood (1 mL), urine and stool samples.

The collection point “0” (PRE) for stool samples should, if possible, be the first stool passed after birth (meconium) and after signing the informed consent form. In the case of premature babies transported from other hospitals, the PRE stool sample should be collected from the first stool passed after obtaining the consent of the guardians to participate in the experiment. Post-FMT samples (“POST”) are samples collected after the second dose of microbiota (FMT2) has been administered, sequentially after 7 days (POST7), 14 days (POST14), 30 days (POST30), 60 days (POST60) and 120 days (POST120).

For the control group, it is assumed that the day identical to the administration of the second dose of microbiota (matching time point) for counting “POST” days is the 6th day of the child’s life.

When collecting feces, at least three (3) fecal samples should be collected from each time point into three separate containers. The sample size should be similar to the size of a cherry, if possible.

Blood and urine should be collected at the following points: 0 (BEFORE), POST14, POST30 and POST120. An effort should be made to correlate these collections with routine collections of material for testing at the clinic in order to minimize the number of procedures and treatments for the newborn within the acceptable time windows (Table 1).

For blood samples, at each of the above-mentioned time points (BEFORE, POST14, POST30, POST120), whole blood (volume 0.5–1.0 mL) and serum (minimum volume 2 × 100 µL = 2 × 0.1 mL) should be collected, and, if a larger volume of serum is obtained, as much of the obtained volume as possible should be secured, divided into 150 µL portions.

For urine samples, at each time point mentioned, one sample (volume 2 mL) should be collected, which should be divided into microtubes of 1 mL each.

Each sample/sample container should be labeled with the patient’s number, date of collection and time point, and then frozen (optimally at −80 °C).

## 5. Expected Results

### 5.1. Primary Outcome

The primary outcome is safety, assessed through adverse event reporting and comparison with the control group.

Examination of the safety profile includes analysis of all adverse events, including any deviations from the norm: deterioration in general condition, appearance of symptoms of infection, and increase in inflammation indicators.

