### 2.2. Trial Design

This will be a safety study of FMT for the prevention of NEC, in the form of a prospective, open-label study with continuous recruitment of up to 40 patients in total (20 in the study group, 20 in the control group). Included patients must meet the exact inclusion criteria described below and must not meet any exclusion criteria. The study group will include 10 premature infants born between 28 0/7 and 36 6/7 weeks of gestation, followed by another 10 premature infants born between 24 0/7 and 27 6/7 weeks of gestation, and 20 premature infants in the control group. After completion of this stage (inclusion and treatment of 20 patients + 20 in the control group), the safety of the therapy will be assessed with a description and presentation of all adverse events, their classification and relationship to the intervention.

The safety of the therapy will be assessed by comparison with a control group, i.e., 20 patients who will meet the same inclusion criteria and will not meet any of the exclusion criteria, subject to the same hospital observation but without undergoing any medical/therapeutic intervention other than the collection of biological material (including stool, blood and urine samples for exploratory testing of the gut microbiota).

Recruitment will occur continuously between January 2026 and January 2027. The study is registered at ClinicalTrials.gov (NCT06333405).

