#### 2.3.1. Sample Size

A formal sample size calculation based on power analysis was not performed, as this is a pilot safety study intended to generate preliminary data (estimates of adverse event rates) for a future randomized controlled trial (RCT). A sample size of 20 subjects in the intervention group was determined based on feasibility constraints and standard recommendations for pilot safety studies, following biostatistical consultation [28]. In the first phase, 10 patients born between 28 0/7 and 36 6/7 will be included, followed by 10 patients born between 24 0/7 and 27 6/7 in the second phase.

The control group will include 20 matched controls—patients who meet the same inclusion and exclusion criteria as the study patients.

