#### 2.3.2. Allocation

During the safety study phase, we plan to enroll the first 20 patients who meet the inclusion criteria and do not meet the exclusion criteria, who will be admitted to the clinic during the study.

The list will be available to all department physicians who will be involved in the study and trained in study procedures. These will also be the individuals who will decide on the administration of FMT to patients and observe them after the procedure.

Patients will be included in the control and study groups in a 1:1 ratio according to the order of admission to the ward. This means that each subsequent patient included in the study will be included in the opposite group to the previous patient.

The study will not be blinded.

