#### 2.3.3. Statistical Analysis

All analyses will be conducted on an intention-to-treat basis.

The primary endpoint is safety, defined as the incidence of adverse events (AEs) and serious adverse events (SAEs) during the observation period.

The proportion of patients experiencing at least one AE or SAE will be compared between groups using Fisher’s exact test. The chi-square test will be applied when its assumptions are met.

The incidence of specific AEs will also be compared using Fisher’s exact test. Relative risks (RRs) with two-sided 95% confidence intervals (CIs) will be calculated.

If the number of events per patient is analyzed, between-group comparisons will be performed using Poisson regression or negative binomial regression, depending on data dispersion.

Time to first AE, if applicable, will be analyzed using Kaplan–Meier estimates and compared using the log-rank test.

Continuous variables will be assessed for normality using the ShapiroWilk test. Normally distributed variables will be compared using Student’s *t*-test, and non-normally distributed variables using the Mann–Whitney U test.

Two-sided tests will be used throughout, with statistical significance set at α = 0.05. Estimates will be presented with two-sided 95% confidence intervals. Analyses will be performed using validated statistical software (e.g., R, Stata, or SAS); the exact software and version will be documented in the final report.

Given the limited sample size, the study is not powered for formal hypothesis testing of small effect sizes. Therefore, interpretation will focus primarily on effect size estimates and their 95% confidence intervals rather than solely on statistical significance. Clinically meaningful differences will be considered in the context of effect magnitude and precision.

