### 4.3. Monitoring the Transplant Recipients After the Procedure

Based on experience with FMT, the highest risk of developing sepsis, a rare but dangerous complication, occurs within the first six hours after the preparation is administered. Therefore, after the procedure, the patient will be continuously monitored.

The following will be assessed for the next 72 h after FMT administration:The number of episodes of oral feeding intolerance, diarrhea and the presence of blood, mucus or pus in the stool.The appearance of symptoms of infection or significant changes in vital signs (ECG, heart function and saturation—continuous measurement; blood pressure—4 times a day; temperature).The number of cases of NEC developed.Observation of other symptoms, such as convulsions, inconsolable crying and anxiety.The number of positive blood cultures and the percentage of antibiotic therapy use.Number of serious adverse events (SAEs), e.g., death, serious threat to health and/or life, and/or deterioration of health.

Blood inflammation parameters (leukocyte count, CRP and procalcitonin) will be collected before administration of the preparation (FMT1) and no later than 6–12 h after administration of FMT2, then every 12–24 h up to 72 h after FMT, depending on the patient’s condition.

A blood culture will be taken in the event of a significant increase in inflammatory parameters.

If any of the above-described criteria for temporary postponement of microbiota administration occur between FMT1 and FMT2 but resolve within 6 h (reassessment of the child’s condition after a minimum of 6 h) and do not recur within the next 6 h, the second dose of microbiota (FMT2) may be administered.

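### Leukocytes, CRP and procalcitonin are measured before and after dosing in both arms, but no outcome uses them on a continuous, baseline-adjusted scale, and the yes/no item that names them is sampled unequally between arms

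*Protocol article*

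**What the plan says.** **Collection.** In the FMT arm (section 4.3), "Blood inflammation parameters (leukocyte count, CRP and procalcitonin) will be collected before administration of the preparation (FMT1"), again by 6–12 h after FMT2, and then every 12–24 h up to 72 h depending on the infant's condition. In controls (section 4.4), a point-0 panel is taken between consent and the fifth day of life. A later panel is due "at least once within 72 h of day 6", or more often if the attending physician sees a need.

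**Outcomes.** Section 5.1 defines the primary safety outcome as all adverse events, "including any deviations from the norm: deterioration in general condition, appearance of symptoms of infection, and increase in inflammation indicators". It gives no cut-off for an increase. The numeric marker limits in section 2.3.6 serve only to postpone dosing or the matching point. Section 5.2 lists hospital stay, weight gain, length of antibiotic therapy and the incidence of other infectious or inflammatory complications. It lists no marker level or change.

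**Analysis (section 2.3.3).** "The incidence of specific AEs will also be compared using Fisher’s exact test", with relative risks and 95% intervals. Event counts per patient and time to first event may also be analysed. A general rule sends continuous variables through a Shapiro–Wilk test to a t-test or Mann–Whitney test, with no variable named. Interpretation is to rest mainly on estimates and their confidence intervals.

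**The concern.** The study is open-label, and section 5.4 concedes detection bias for subjective endpoints. Laboratory values are among the least subjective safety measures collected. If their only named use is as a yes/no event, two infants just above and far above the cut count the same, and the point-0 value does nothing beyond helping to define an increase. A real inflammatory response to FMT would then be hard to see with 20 infants per arm.

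There is also a risk in the other direction. An any-increase item depends on how often one looks, and the two arms are looked at with different frequency. The comparison could show an excess in the FMT arm that comes from the sampling schedule alone.

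**Working it through.** **Inputs from the protocol article.**
- Size (2.2): "continuous recruitment of up to 40 patients in total (20 in the study group, 20 in the control group").
- Test level (2.3.3): "Two-sided tests will be used throughout, with statistical significance set at α = 0.05".
- Allocation (2.3.2): "Patients will be included in the control and study groups in a 1:1 ratio according to the order of admission to the ward".
- Attrition (5.3): about 15%, so 20 × 0.85 = 17 per arm.
- Power (2.3.1): "A formal sample size calculation based on power analysis was not performed". There is therefore no stated power figure to reproduce.

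**Assumptions, not in the article.** The marker is normal after log transformation. The true shift d is 0.5 to 1.2 SD. Between 5% and 50% of controls exceed the cut-off for an increase. The correlation ρ between point-0 and later values is 0.5 (range 0.3 to 0.7).

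**Formulas.**
- t-test: noncentral t, noncentrality d√(n/2), df 2n − 2.
- ANCOVA: the same with d/√(1 − ρ²) in place of d, df 2n − 3.
- Fisher: exact enumeration. If a share p of controls exceeds the cut c = Φ⁻¹(1 − p), then 1 − Φ(c − d) of FMT infants exceed it.

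**Worked case, n = 20, d = 0.8.**
- t-test: noncentrality 0.8 × √10 = 2.53, power 69%.
- ANCOVA, ρ = 0.5: 0.8/0.866 = 0.924, noncentrality 2.92, power 81%.
- Fisher, p = 20%: c = 0.842, FMT proportion 1 − Φ(0.042) = 48%, power 37%. For p = 5%, 10%, 30% and 50%, power is 17%, 28%, 37% and 37%.

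**Across shifts, n = 20.**

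| Shift (SD) | Fisher | t-test | ANCOVA, ρ = 0.5 | Fisher as share of t-test |
|---|---|---|---|---|
| 0.5 | 4–15% | 34% | 43% | 11–44% |
| 0.8 | 17–37% | 69% | 81% | 24–54% |
| 1.0 | 33–56% | 87% | 95% | 38–65% |
| 1.2 | 53–74% | 96% | 99% | 55–77% |

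**Shift detectable with 80% power.**
- n = 20: Fisher 1.30–1.51 SD; t-test 0.91 SD; ANCOVA 0.87, 0.79 and 0.65 SD at ρ = 0.3, 0.5 and 0.7.
- n = 17: Fisher 1.38–1.64 SD; t-test 1.00 SD; ANCOVA 0.86 SD at ρ = 0.5.

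**The same point as precision.** Suppose 8/20 FMT infants and 4/20 controls show an increase. The relative risk is 2.0 and SE(log RR) = √(1/8 − 1/20 + 1/4 − 1/20) = 0.524, so the 95% CI is 0.72 to 5.59. On the normal scale these rates correspond to a shift of 0.842 − 0.253 = 0.59 SD. Estimated from the two proportions, its SE is √[0.16/(20 × 0.280²) + 0.24/(20 × 0.386²)] = 0.427, a half-width of 0.84 SD. ANCOVA at ρ = 0.5 gives a half-width of 2.026 × √(2/20) × 0.866 = 0.55 SD. The yes/no interval is about 1.5 times as wide for the same infants and the same blood.

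**Unequal sampling.** A first panel at 12 h and then every 24 h gives panels at 12, 36 and 60 h, so three. A first panel at 6 h and then every 12 h gives six by 66 h. Controls need one. If each panel has an assumed 5% chance of an incidental increase, independently, then 1 − 0.95^k is 5% for one panel, 14% for three, 19% for four and 26% for six. Out of 20 infants that is 1 expected control against about 3 to 5 FMT infants, with no effect of FMT at all. Positive correlation between panels would shrink this gap; a higher per-panel chance would widen it.

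**The case against.** **The general rule for continuous variables may already cover the markers.** This stands in part. A reader might infer that the markers can enter the analysis only as yes/no; the article does not say so. But the rule commits to no marker and no time point, and even where applied it gives an unadjusted comparison that leaves the point-0 value unused.

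**This is detail for an unseen analysis plan.** Transformations and detection-limit rules are. Which measurements are outcomes, and on what scale, is something the article itself sets out in 5.1 and 5.2.

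**The trial claims no power.** Correct, and no stated figure is wrong. The article puts estimates and intervals first, but the precision calculation shows that the loss applies there too.

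**The gain rests on assumptions.** It does. Postponing dosing or the matching point when markers are raised narrows the range of pre-dose values and may lower ρ. At ρ near zero, ANCOVA falls back to roughly the t-test (0.91 SD), still well below 1.30 SD.

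**A comparison near 72 h cannot be made from the schedule as written.** This stands. The control panel may fall at any time within 72 h of day 6. FMT is given on days 3–6, or up to day 14, so times and ages differ. A common window is needed first.

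**Detection bias is already addressed.** Section 5.4 cites CRP levels among its objective definitions for sepsis and NEC. A reader might infer that unblinded staff decide at will what counts as an increase; the article does not state that. It simply gives no cut-off for that item.

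**Conclusion.** The point holds in this form: no continuous marker outcome is specified, although pre- and post-dose values exist in both arms. At a 0.8 SD shift, Fisher's test on the yes/no item has about 17–37% power, against 69% for a t-test and 81% for ANCOVA. The shift detectable with 80% power is about 1.3–1.5 SD for Fisher and about 0.65–0.87 SD for ANCOVA (ρ from 0.7 to 0.3). All of these rest on the assumed log-normality, shift, cut-off and correlation.

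A reader might infer that most of the available power is always lost. That is too strong. Relative to the t-test, the loss is 46–76% at 0.8 SD but 23–45% at 1.2 SD.

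The unequal number of panels is a separate weakness of the same item and does not depend on the power assumptions. Its direction is clear, towards more recorded increases in the FMT arm; its size is not known from the article. Neither weakness undermines the clinical AE/SAE endpoint as such. A marker analysis would supplement that endpoint, not replace it.

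**What to change.** 1. In 5.2 and 2.3.3, add log CRP, log procalcitonin and leukocyte count as secondary safety outcomes. Compare the arms by ANCOVA with the point-0 value and age at sampling as covariates. Report ratios of means (log markers) or a difference of means (leukocytes) with 95% CI. State that the three comparisons are estimates, with no claim of confirmatory testing.
2. In 4.4, place the one control panel already required in a fixed window after the matching point that corresponds to one of the FMT-arm panels. Use only that common window for the comparison.
3. Keep increases in inflammation indicators as a descriptive adverse-event listing, with the number of panels per infant shown by arm.

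**Cost.** No extra blood draw is needed beyond the required panels. The control window becomes slightly tighter, and a rule is needed for values below the detection limit. Age at sampling partly separates the arms by design, so adjusting for it costs some precision. If age explained 25% of the variation in arm (an assumption), the ANCOVA detectable shift at ρ = 0.5 would rise from 0.79 to about 0.79/√0.75 = 0.91 SD. That is still below the 1.30 SD at best for Fisher's test. Because allocation is by alternation, the adjusted estimate remains open to the residual confounding that section 5.4 already acknowledges.
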